### Sample size

According to a previous study that investigates the therapeutic effect of acupuncture for asthma [23], the mean improvement of the AQLQ was − 2.75 ± 4.52 (mean ± SD) in the acupuncture group and 0.86 ± 4.95 in the control group. With a two-side significance level of α = 0.05 and power of 80%, 27 participants are required in each group. Allowing for a 20% dropout rate, 34 participants per treatment arm will be recruited, equaling 68 patients in total.

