## Method and design

### Study design

A two-arm, multi-center, randomized controlled trial will be conducted at the First Affiliated Hospital of Chengdu University of Traditional Chinese Medicine (CDUTCM) and the First Affiliated Hospital of Anhui University of Traditional Chinese Medicine. Sixty-eight eligible asthma patients diagnosed with the guide for asthma management and prevention of updated GINA 2019 [2] will be recruited and randomized into two groups with a 1:1 ratio. Outcome assessment will be performed at the baseline and the end of treatment and during the follow-up period. Patients enrolment will be started in November 2019 and is expected to end in October 2021. The details of the study design are shown in Fig. 1.

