## Discussion

This is the first RCT focused on the efficacy differences of the acupoints on the Lung meridian compared to the acupoints on the Heart meridian for treating chronic persistent asthma. The results will provide evidence for acupuncture prescription selection and the clinical efficacy improvement. The results of this trial will also be used to determine whether or not a full definitive trial will go ahead, which will further confirm the theory of Meridian-viscera Association.

The theory of Meridian-viscera Association emphasizes the diagnostic and therapeutic values based on the mutual relation in physiology and pathology between meridians and viscera. That is, visceral physiological functions and pathological changes will manifest in the corresponding meridians or the acupoints [34], and the visceral disorders can be treated with the involved meridian and acupoints [35]. The lung is close to the heart anatomically, so the two viscera have close association physio-pathologically. Based on the theory of Meridian-viscera Association and clinical practice, the Lung meridian and the Heart meridian are the commonly used meridians for pulmonary disorders including asthma [17, 18]. Hence, this study will select Taiyuan (LU9), Lieque (LU7), and Chize (LU5) on the Lung meridian and Shenmen (HT7), Yinxi (HT6), and Shaohai (HT3) on the Heart meridian for the following reasons: (1) these acupoints have been proved to be effective in improving QoL and relieving symptoms of asthma patients [18, 23], (2) all of these acupoints are specific acupoints on the two meridians, and (3) the selected acupoints are on the medial side of the upper arm and at the same nerve segment based on the modern anatomy so as to minimized the bias of comparison.

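### The stated 80% power is not supported for Lung versus Heart meridian acupuncture, because it rests on an acupuncture-versus-control difference from another study.

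*Protocol article*

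**What the plan says.** The Sample size section of the protocol article opens "According to a previous study that investigates the therapeutic effect of acupuncture for asthma" and reports from that study that "the mean improvement of the AQLQ was − 2.75 ± 4.52 (mean ± SD) in the acupuncture group", against "0.86 ± 4.95 in the control group". It continues: "With a two-side significance level of α = 0.05 and power of 80%, 27 participants are required in each group". Then: "Allowing for a 20% dropout rate, 34 participants per treatment arm will be recruited, equaling 68 patients in total". No other effect assumption appears in the article.

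The comparison being made is described elsewhere. Under Study design, patients "will be recruited and randomized into two groups with a 1:1 ratio". Under Acupuncture interventions, both groups receive 12 sessions of manual acupuncture at three bilateral points, on the Lung meridian in one group and on the Heart meridian in the other. There is no sham, waiting-list or medication-only arm. The Data analysis section makes the between-group ANCOVA of AQLQ change from baseline to week 4 the main comparison.

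The Discussion justifies the chosen points of both meridians by saying that "these acupoints have been proved to be effective in improving QoL and relieving symptoms of asthma patients". It cites two references for this, and one of them is the study that supplied the sample-size figures. The Discussion also says: "The results of this trial will also be used to determine whether or not a full definitive trial will go ahead".

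**The concern.** The planning difference measures acupuncture against something the article calls a control group. Using it as the Lung-versus-Heart difference amounts to assuming that Heart meridian acupuncture performs about as the control group did in that study. That sits badly with the article's own case that the points on both meridians work, a case that relies on the same study. The article gives no expected difference between the prescriptions and no reason why the acupuncture-versus-control difference should carry over.

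Two things are at stake. A reader of the stated power will believe that the trial has a four-in-five chance of detecting a difference that matters between the prescriptions, and nothing in the article supports that. The result is also meant to inform both the choice of prescription and whether a definitive trial follows. If the true difference is smaller than the planning value, an inconclusive result becomes more probable than the stated power suggests, and such a result is easily misread.

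**Working it through.** **Inputs (Sample size section).** Changes −2.75 (SD 4.52) and 0.86 (SD 4.95); two-sided α 0.05; power 80%; 27 per group; 20% dropout; 34 per arm.

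**Reproducing the plan's figure.**
- Difference: 0.86 − (−2.75) = 3.61.
- Pooled SD: √[(4.52² + 4.95²)/2] = 4.74.
- Standardised difference: 3.61/4.74 = 0.762.
- Normal approximation: n = 2 × [(1.96 + 0.8416)/0.762]² ≈ 27.06 per group. At n = 27 the power is 79.9% (normal approximation) or 78.4% (noncentral t).
- Dropout: 27/0.80 = 33.75, rounded up to 34 per arm, 68 in total.

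The stated 27, 34 and 68 therefore follow from the stated inputs, to within rounding. The question is whether those inputs belong to this comparison.

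**Power if the prescriptions differ by less.** The fractions below are assumptions chosen to show a range. Only the SD and the sample sizes come from the protocol. Two-sample t test, two-sided 0.05, noncentrality d√(n/2), SD 4.74:

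| Lung–Heart difference | Fraction of 3.61 | d | Power, 27 per arm | Power, 34 per arm |
|---|---|---|---|---|
| 3.61 | 100% | 0.762 | 78% | 87% |
| 2.71 | 75% | 0.571 | 54% | 64% |
| 1.81 | 50% | 0.381 | 28% | 34% |
| 0.90 | 25% | 0.190 | 11% | 12% |

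At half the planning difference, 80% power would need about 109 evaluable patients per arm (normal approximation). With 20% dropout that is 109/0.80, or 137 recruited per arm and 274 in total.

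**Precision with the planning SD.** The half-width of the 95% confidence interval is t × 4.74 × √(2/n): about 2.6 at 27 per arm and 2.3 at 34 per arm.

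**Scale check.** The Primary outcome section defines the AQLQ score as the mean of 32 seven-point items, with higher scores better and a minimum clinically important difference of 0.52. The planning difference is 3.61/0.52 ≈ 6.9 times that value, and the acupuncture group's improvement is negative. The planning figures therefore fit this scale poorly. The table's percentages depend only on d, but what d means in AQLQ points depends on an SD that the article does not give for this scale. With assumed SDs of 0.69, 0.75 and 1.0, t-test power for a difference of 0.52 is 78%, 71% and 47% at 27 per arm, and 86%, 80% and 56% at 34 per arm. With SD 4.74 it is about 7% at 27 per arm.

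**The case against.** A reader might infer that the trial lacks 80% power, or that its power is well below 80%. The documents do not support that. Power depends on the true Lung–Heart difference, which the article does not give. The Background says that the Lung meridian connects with the lung directly and the Heart meridian only indirectly, so a difference is anticipated, and being effective does not mean being equally effective. The article also does not say what the control group of the cited study received. The scale check cuts the same way: if the SD of AQLQ change were near 0.7, 68 patients would give about 80% power for the minimum important difference. All of this stands, and it limits the point to a lack of support for the figure.

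A reader might also infer that a non-significant result will be reported as equal efficacy, or that the decision on a definitive trial rests on significance. The article says neither. Data analysis already promises effect estimates with confidence intervals, and the prospect of a definitive trial means that this need not be the last test. That softens the consequence, but the Sample size section still claims 80% power without condition.

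Covariate adjustment does not close the gap at the smaller differences. To bring half the planning difference back to d = 0.762, the residual SD would have to halve, so the covariates would have to explain 1 − 0.5² = 75% of the variance. Nothing suggests that age, gender, disease duration, expectation and centre do so.

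That an article condenses a fuller protocol is no answer either. The basis of the calculation is stated, and it belongs to a different comparison.

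**Conclusion.** The point holds in limited form. The 80% power is unsupported for Lung versus Heart, because its only basis is an acupuncture-versus-control difference of 0.76 SD, while both arms here receive acupuncture at points the article regards as proved effective on the strength of the same study. The arithmetic is correct, and the figure would apply if the prescriptions truly differed by about 0.76 SD. At three quarters, half and a quarter of that, power is about 54%, 28% and 11% with 27 per arm, or 64%, 34% and 12% with 34. These figures assume the planning SD and an unadjusted t test, and the fractions are illustrative. The conclusion does not depend on any one of them: no expected difference between the prescriptions is stated, so no power for that difference has been justified.

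**What to change.** Amend the Sample size section in one of three ways:

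1. State that 68 patients give about 80% power only if the two prescriptions differ by about 0.76 SD, and show the power for smaller differences as explicit assumptions, as in the table above.
2. State and justify a target difference between the prescriptions on the AQLQ scale defined under Primary outcome, with an SD for that scale, and give the power that 68 patients provide for it. The scale and sign of the source figures should be checked at the same time.
3. Present 68 as a pilot size, give the expected width of the confidence interval, and drop the 80% claim.

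Under any of these, add that a non-significant result will not be taken as equal efficacy and that the result will be interpreted from the confidence interval. Do not add a rule that needs the whole interval to lie within ±0.52. With the planning SD the half-width is 2.3 to 2.6, so such a rule could never be met.

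The cost is wording only. The number of patients, the visits and the analysis model stay as they are. The stated power becomes conditional and less favourable, and the conclusions more cautious.

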### Outcome measurements

#### Primary outcome

##### Asthma Quality of Life Questionnaire (AQLQ)

In this study, the standard version of AQLQ will be used [24]. This questionnaire measures the functional problems that are most troublesome to adults with asthma over the 2 weeks prior to the interview. The AQLQ contains 32 items: activity limitation (11 items), symptoms (12 items), mental health (5 items), and environmental stimuli (4 items). Responses are rated on 7-point Likert scales for every item. High scores indicate a better health-related quality of life. The mean score of all 32 items is the overall AQLQ score. The minimum clinically important difference for AQLQ has been reported as 0.52 [25].

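### The AQLQ figures behind the sample size are not reconciled with the AQLQ endpoint the protocol defines, so the stated 80% power is not established for that endpoint

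*Protocol article*

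**What the plan says.** The Sample size section of the protocol article takes its inputs from one earlier trial: "According to a previous study that investigates the therapeutic effect of acupuncture for asthma". It reports that "the mean improvement of the AQLQ was − 2.75 ± 4.52 (mean ± SD) in the acupuncture group", and the same sentence gives the SD and the control values as "4.52 (mean ± SD) in the acupuncture group and 0.86 ± 4.95 in the control group". It then states: "With a two-side significance level of α = 0.05 and power of 80%, 27 participants are required in each group". The dropout step follows: "Allowing for a 20% dropout rate, 34 participants per treatment arm will be recruited, equaling 68 patients in total".

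The primary outcome section describes 32 items on seven-point scales and defines the score: "High scores indicate a better health-related quality of life. The mean score of all 32 items is the overall AQLQ score". It adds: "The minimum clinically important difference for AQLQ has been reported as 0.52". The Data analysis section makes the change in AQLQ from baseline to week 4 the outcome variable of the main ANCOVA.

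Nowhere does the article rescale the planning figures, explain their sign, or give an SD for change in the item-mean score.

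**The concern.** A reader who puts the planning figures on the scale defined for the primary outcome meets three difficulties: an improvement with a negative sign on a scale where higher is better, a difference larger than half the scale, and SDs close to the limit the scale allows. If the figures come from another instrument or another scoring, the 80% does not describe power for the endpoint that will be analysed.

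This has a practical consequence. The abstract and the Discussion both say that the results will help decide whether a definitive trial follows. A null result read as the product of an 80%-powered comparison could carry more weight in that decision than the design supports.

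**Working it through.** **1. Reproduce the plan's figure.** Inputs from the Sample size section: means −2.75 and 0.86, SDs 4.52 and 4.95, two-sided α = 0.05, power 80%. Allocation is 1:1 (Study design).

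- Difference: 0.86 − (−2.75) = 3.61
- Pooled SD: √[(4.52² + 4.95²)/2] = √[(20.43 + 24.50)/2] = 4.74
- Standardised effect: 3.61/4.74 = 0.762
- n per group: 2 × (1.960 + 0.842)²/0.762² = 27.06
- Dropout: 27/(1 − 0.20) = 33.75, so 34 per arm and 68 in total

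Power at 27 per group is 79.9% by the normal approximation and 78.4% by the noncentral t. The calculation is sound; the question is only about its inputs.

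**2. Put the inputs on the defined scale.** The mean of seven-point items spans 6 units, so change lies between −6 and +6.

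- Direction: with higher scores better, a change of −2.75 is a worsening, although the text calls it an improvement.
- Size: 3.61/0.52 = 6.9 times the MCID; 3.61/6 = 60% of the scale width.
- Spread: for a variable bounded by ±6 with mean m, the largest possible SD is √[(6 − m)(6 + m)].
  - Acupuncture: √(8.75 × 3.25) = 5.33; 4.52/5.33 = 85%.
  - Control: √(5.14 × 6.86) = 5.94; 4.95/5.94 = 83%.
  - These ceilings are reached only if every patient moves from one end of the scale to the other.

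**3. Try the item-sum reading.** Dividing by 32 gives a difference of 3.61/32 = 0.11 per item and an SD of 4.74/32 = 0.15. The MCID on the sum would be 0.52 × 32 = 16.64, so 3.61 is about one fifth of it. This reading does not match the endpoint either.

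**4. What 27 evaluable per arm gives on the item-mean scale.** The protocol states no SD of change on this scale, so the SDs below are assumptions. The method is an unadjusted two-sample t test, two-sided 0.05. The difference detectable with 80% power is 0.777 SD, so power for 0.52 reaches 80% at SD = 0.52/0.777 = 0.67.

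| Assumed SD of change | Power for 0.52 | Difference detectable with 80% power (0.777 × SD) |
|---|---|---|
| 0.6 | 88% | 0.47 |
| 0.67 | 80% | 0.52 |
| 0.7 | 76% | 0.54 |
| 0.8 | 65% | 0.62 |
| 1.0 | 47% | 0.78 |
| 1.2 | 35% | 0.93 |

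**The case against.** Several points on the other side are fair.

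- **Implausible is not impossible.** The stated SDs lie below their ceilings. Second moments of 4.52² + 2.75² = 28.0 and 4.95² + 0.86² = 25.2, against a maximum of 36, could arise if about 78% and 70% of patients made a full swing and the rest did not change. A reader might infer that the figures are proven to come from another scale. They are not: the cited study is not at hand, and the mismatch is a strong inference. What stands is that the article prints figures and a scale definition that it does not reconcile.
- **The sign has no effect on n.** Only the absolute difference enters, and the source may have subtracted follow-up from baseline. A reader might infer that the planning data show acupuncture doing harm; the documents do not support that. The unexplained sign is still a contradiction in the text.
- **Power depends on the standardised effect.** A mismatch of units does not show that 27 is too few, and the protocol never makes 0.52 its design target. A reader might infer that true power is below 80%. That does not follow, because the protocol gives no SD on this scale and power for 0.52 exceeds 80% if the SD is below about 0.67. The planned ANCOVA may also reduce the residual SD.
- **The protocol's SD cannot be paired with its MCID.** Power for 0.52 computed with an SD of 4.74 would be very low, but it combines figures that probably belong to different scales and should not be used.

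The condensed format of an article is no answer here. Nothing is being asked for that was left out; the printed figures conflict with each other.

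**Conclusion.** The sample-size paragraph is wrong as written, in its inputs and not in its arithmetic. The 27 per arm, and hence the 34 and the 68, follow correctly from a 0.76 SD effect. That effect cannot credibly be placed on the week-4 change in the item-mean AQLQ, either as printed or as an item sum, so the 80% is not established for the primary endpoint.

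The conclusion about the mismatch rests only on figures in the protocol. The size of the power consequence rests on assumed SDs: for a difference of 0.52, power with 27 evaluable per arm runs from 88% at SD 0.6 to 35% at SD 1.2. Whether the trial is adequately powered remains open, and no larger sample is shown to be necessary.

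**What to change.** Keep 68 patients and rewrite the Sample size section in units of the primary endpoint.

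1. State the instrument, scoring and direction of change behind −2.75 and 0.86, or remove these figures.
2. State an assumed between-group difference and an assumed SD for week-4 change in the item-mean AQLQ, say where each comes from, and relate the difference to 0.52.
3. Replace the unqualified 80% with the statement that 27 evaluable patients per arm give 80% power for a 0.78 SD difference (unadjusted t test, two-sided 0.05).
4. Show power at 0.52 over a range of assumed SDs on both sides of the 0.67 threshold, as in the table above.

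The cost is a rewritten paragraph, with no extra patients and no change to endpoint or analysis. The drawback is that the stated power may become less favourable.

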### Inclusion criteria

Patients fulfilling the following 7 items will be included: (1) aging from 18 to 65 years, (2) diagnosed as chronic persistent asthma by respiratory physicians according to the guide of GINA 2019 and medical history, (3) having mild or moderate asthma according to the GINA 2019, (4) having increased in the FEV1 of > 12% and > 200 mL from the pre-bronchodilator value, (5) the FEV1/forced vital capacity (FVC) < 70%, (6) without participating in any other clinical trials or receiving acupuncture due to asthma within 1 month, and (7) having signed informed consent.

### Exclusion criteria

Patients who match any of the following 8 items will be excluded: (1) be hospitalized in intensive care unit due to acute exacerbation of asthma in the previous 3 months (representing patients at highest risk of adverse asthma outcomes); (2) be diagnosed as other pulmonary diseases such as bronchiectasis, tuberculosis, abscess, cystic fibrosis, alpha 1 antitrypsin deficiency, or restrictive lung disease; (3) having serious cardiovascular diseases such as uncontrolled heart failure, coronary disease, myocardial infarction, severe hypertension, or uncontrolled arrhythmia; (4) having other uncontrolled diseases including liver or kidney or hematopoietic diseases, endocrine and immune diseases, mental disorders, and malignancy; (5) asthma occurs only when accidentally exposed to allergens or chemical sensitizers; (6) having lower respiratory tract infection (e.g., pneumonia) or taking systemic glucocorticoids more than 10 days for severe acute asthma attacks within 1 month before enrollment; (7) currently be pregnant or breast feeding at the time of enrolment or planned pregnancy within the study period; or (8) having any acupuncture contraindications, such as serious atopic, infectious dermatopathy, thrombocytopenic purpura, or hemophilia.

### Acupuncture interventions

The acupuncture treatment of each group will consist of 12 sessions of 30 min duration, each administered over a period of 4 weeks (three sessions per week). All the acupuncture manipulation will be performed by licensed acupuncturists with at least 5 year’s clinical experience.

The manual acupuncture stimulation will be performed at bilateral Taiyuan (LU9), Lieque (LU7), and Chize (LU5) for patients in group A, and manual acupuncture stimulation will be performed at bilateral Shenmen (HT7), Yinxi (HT6), and Shaohai (HT3) for patients in group B (Fig. 2).

**Fig. 2 Fig2:**
[figure not shown]
Locations of acupoints. *Acupoints on Lung meridian—*Chize (LU5): on the cubital crease, on the radial side of the tendon of biceps brachii; Lieque (LU7): on the radial margin of the forearm, 1.5 cun above the transverse crease of the wrist, between the brachioradial muscle tendon and the long abductor muscle tendon of thumb; and Taiyuan (LU9): on the radial side of the transverse crease of the wrist, where the radial artery pulsates. *Acupoints on Heart meridian*—Shaohai (HT3): at the midpoint of the line connecting the medial end of the transverse cubital crease with the medial epicondylus of the humerus; Yinxi (HT6): on the palmer side of the forearm, the point is on the radial side of the tendon of the flexor carpi ulnaris, 0.5 cun above the transverse crease of the wrist; and Shenmen (HT7): on the wrist, at the ulnar end of the transverse crease of the wrist, in the depression on the radial side of the tendon of the flexor carpi ulnaris

The acupuncture manipulation of these two groups is as follows: the disposable sterile filiform needles (0.25 × 25 mm, 0.35 × 40 mm; Huatuo Medical Instrument Co., Ltd., China) will be inserted into acupoints with the depth of 10–30 mm after skin disinfection by alcohol. Manipulations of twirling, lifting, and thrusting will be performed in order to induce *deqi* sensation. Then needles will be retained at the acupoints for 30 min. In order to maintain the *deqi* sensation, the above procedures will be manipulated intermittently during the 30 min.

### Medications

Patients can use the inhaled doctor-directed Seretide (salmeterol and fluticasone) or Symbicort (formoterol and budesonide) as conventional therapy following the respiratory physicians’ instruction. Participants will be not allowed using other interventions during this trial but will be permitted to use inhaled salbutamol or other medication advised by doctors in an emergency. The name of medications, specifications, dose, duration of use, time of symptom relief, etc. will be recorded in details.

There should be at least 6 h between the use of salbutamol and lung function measurements. A stable dose of inhaled glucocorticoids and antihistamines should be maintained for at least 2 months prior to enrollment and during this study. If patients’ desensitization therapy is in the “maintenance” phase, the medication used should be maintained at a stable dose of at least 1 month prior to the enrollment and during this study. Short courses of antihistamine therapy or inhaled glucocorticoid therapy are allowed to treat hay fever. Short-term (< 10 days) use of systemic corticosteroids, aerosol therapy (including β2-agonists, anticholinergics, and steroids), and antibiotic therapy will be permitted during this study.

